### Objectives {10}

The study will be guided by the following specific objective: To determine whether the outcomes of dynamic balance, postural stability, gait biomechanics, and joint function improve in the intervention group and the balance training group after a 6-week intervention period and whether there is a significant difference compared to the control group.

The study is also based on the following hypotheses:The intervention group and the balance training group will lead to similar significant improvements in outcomes compared to the control group.It is also hypothesized that there will be no significant differences between the intervention group and the balance training group.

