### Trial design {12}

This study protocol follows the “Standard Protocol Items: Recommendations for Interventional Trials (SPIRIT) 2013 Statement” (https://www.equator-network.org/reporting-guidelines/spirit-2013-statement-defining-standard-protocol-items-for-clinical-trials/). The study is a prospective, single-center, interventional, randomized controlled trial with an intervention group (forefoot and rearfoot stability training) and two comparison groups, either a usual balance training group or a control group. It is a single-blind (principal investigator) design with patients randomized 1:1:1 to one of the three parallel groups. To ensure internal validity, a control group is included that does not receive any balance training intervention. Because many patients with CAI do not seek medical or physical therapy and continue with their usual activities, participants in the control group are allowed to do so. A summary of study information is presented in Table 1.

**Table 1 Tab1:** Study information

Category	Information
Country	Germany
Intervention	Active part: 6 weeks of training with the Mini Stability Trainer according to a predefined exercise schedule; 6 weeks of training with the Wobble Smart Board according to a predefined exercise schedule; one training session is performed under the supervision of a member of the study team, at least 17 training sessions are performed independently by each subject at home Control group: activities of daily living and sports activities; balance exercises are not allowed
Inclusion and exclusion criteria	Inclusion criteria: age between 18 and 44 years; based on the guidelines of the International Ankle Consortium: history of at least one ankle injury more than 1 year ago with typical signs of inflammation; self-reported ankle instability; in addition, two or more episodes of “giving way” must have occurred within the previous 6 months; Cumberland Ankle Instability Tool (CAIT ^a^) score ≤ 24 (in the case of bilateral ankle instability, the more severely affected side is selected) Exclusion criteria: acute injury, surgery or fracture of the lower extremity, neurological disorders, chronic overuse injuries such as Achilles or patellar tendinopathy; current participation in a targeted ankle rehabilitation program

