### Sample size {19}

An a priori sample size estimation based on the results of pilot measurements [40] examining change in dynamic balance after 6 weeks of balance training using the Mini Stability Trainer indicated that 33 participants (11 per group) would be needed to detect a mean difference of 4.6% in the composite score of the YBT with an effect size of *f* = 0.33 and a probability of 1 − *β* = 0.9 at a significance level of *α* = 0.05. To account for potential dropouts and loss to follow-up, the target number of participants is 36 (12 per group).

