## Statistical methods

### Statistical methods for primary and secondary outcomes {27a}

Primary and secondary outcome measures are reported descriptively using mean ± SD or median and interquartile range according to their type (e.g., ordinal or interval scale). After testing the data for normal distribution using the Shapiro-Wilk test and histograms, for the primary outcomes of dynamic balance (YBT) and postural stability (MBESS), the significance of differences in post-intervention change within and between groups will likely be analyzed using repeated measures analysis of variance (ANOVA) (YBT) or Friedman tests or Kruskal-Wallis tests (MBESS) and post hoc tests with Bonferroni correction to account for multiple testing. After testing the data for normal distribution using the Shapiro-Wilk test and histograms, for the secondary outcome of gait biomechanics, the significance of differences in post-intervention change within and between groups will likely be analyzed using repeated measures analysis of variance (ANOVA) and post hoc tests with Bonferroni correction to account for multiple testing. For the secondary outcome of joint function (FAAM), the significance of differences in post-intervention change within and between groups will be analyzed using Friedman tests or Kruskal-Wallis tests and post hoc tests with Bonferroni correction to account for multiple testing. The global significance level is set to *α* = 0.05. No additional analyses are planned.

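### Bonferroni after the omnibus test is valid but needlessly conservative with three arms: within one outcome, a closed test holds the same familywise error with more power

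*Protocol article*

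**What the plan says.** The trial has "patients randomized 1:1:1 to one of the three parallel groups" (item 12). Item 27a plans repeated-measures ANOVA for the YBT and rank-based omnibus tests for the MBESS. These are followed by post hoc tests with Bonferroni correction; the MBESS wording is "Friedman tests or Kruskal-Wallis tests (MBESS) and post hoc tests with Bonferroni correction to account for multiple testing". Gait and FAAM receive the same treatment. The section adds: "The global significance level is set to *α* = 0.05". It does not say how many tests form the Bonferroni family, or whether the 0.05 applies to each primary outcome or to both together.

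The first hypothesis in item 10 expects both training arms to improve more than control. The second expects that "there will be no significant differences between the intervention group and the balance training group". Item 9b calls the comparison of the two devices the primary objective.

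Item 19 sizes the trial on the YBT: "33 participants (11 per group) would be needed" for a "mean difference of 4.6% in the composite score of the YBT with an effect size of *f* = 0.33", with "a probability of 1 − *β* = 0.9" "at a significance level of *α* = 0.05". The target is 36, or 12 per group. No power is given for any pairwise contrast.

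**The concern.** The omnibus test and the Bonferroni division each protect against the same false claims. When there are exactly three arms, the first already does the whole job for one between-arm comparison. The second then lowers the pairwise threshold to 0.05/3 = 0.0167 without being needed to hold 5% within that comparison.

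The planned power of 0.9 belongs to the omnibus test. The first hypothesis needs two pairwise results, both training arms against control, and these are where the stricter threshold bites. It also makes a real difference between the devices harder to detect, and that is the comparison item 9b puts first. With 12 per arm there is little power to give away.

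**Working it through.** **Step 1. Why the closed test holds alpha.** The possible null patterns among three arms are few.
- All three equal: a false pairwise claim requires a false omnibus rejection, which has probability alpha.
- Exactly two equal: only one pairwise null is true. Testing it at alpha errs with probability at most alpha.

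So omnibus at alpha, then each pair at alpha, has familywise error of at most alpha within one outcome's between-arm comparison. This does not depend on any effect size.

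**Step 2. Reproduce the planned sample size.** Inputs from item 19: f = 0.33, alpha = 0.05, power 0.9, N = 33; three groups; two YBT measurements (item 16). Assumption not in the article: pre-post correlation rho = 0.5. For the group-by-time interaction:

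lambda = f² × N × 2/(1 − rho) = 0.1089 × 33 × 2/0.5 = 14.37, with df 2 and 30.

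The noncentral F gives power 0.9075 at N = 33 and 0.874 at N = 30, so 33 is reproduced. Of the values tried, only rho = 0.5 does this: rho = 0.3 needs N = 45 and rho = 0.7 needs N = 21.

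**Step 3. Convert to change scores.** With control at 0 and both training arms at d (in SD of change), lambda = n × (2/3) × d². Hence d = √(1.5 × 14.37/11) = 1.40.

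**Step 4. Compare the two rules.** Simulation of 400,000 trials per scenario, with normal change scores, pooled variance and df = 3n − 3. Both rules require the omnibus test to reject at 5%. Pairs are then tested at 0.05/3 (plan, assuming three pairs) or at 0.05 (closed test).

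| Setting | One training arm vs control: plan → closed | Both vs control: plan → closed |
|---|---|---|
| 12 per arm, rho 0.5 | 0.811 → 0.892 (+8 points) | 0.707 → 0.851 (+14) |
| 11 per arm, rho 0.5 | 0.768 → 0.860 (+9) | 0.650 → 0.811 (+16) |
| 11 per arm, rho 0.3 | 0.597 → 0.710 (+11) | 0.445 → 0.635 (+19) |
| 11 per arm, rho 0.7 | 0.949 → 0.979 (+3) | 0.912 → 0.969 (+6) |

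A noncentral t check at 11 per arm, without the omnibus gate, gives 0.768 at 0.0167, in agreement with the plan's figure.

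**Step 5. Device comparison.** Half the planning effect is 1.40/2 = 0.70 SD. With means (0, 0.70, 1.40) and 12 per arm, the Mini-versus-Wobble difference is found with power 0.23 under the plan and 0.38 under the closed test.

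**Step 6. Error rates within one outcome.** All arms equal: plan 0.042, closed 0.050. Two arms equal and the third shifted: plan 0.017, closed 0.050.

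**Step 7. Two primary outcomes.** Treat the outcomes as independent and suppose both hypotheses are true. The chance of a false device claim on either primary is then 1 − (1 − 0.017)² = 0.033 under the plan, and 1 − 0.95² = 0.0975 under the closed test at 0.05 per outcome. At 0.025 per outcome, the closed test's total is at most 0.025 + 0.025 = 0.05. Its power at 12 per arm is then about 0.82 per contrast and 0.76 for both, against the plan's 0.81 and 0.71.

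**Step 8. Rank tests, indicative only.** The article gives no MBESS effect size. Assuming a normal shift of 1.4 SD and 11 per arm, Kruskal-Wallis followed by pairwise rank-sum tests goes from 68% to 82% per contrast and from 53% to 75% for both, with familywise error no higher than 4.8%. The real score is bounded between 0 and 30, so these figures show direction rather than size.

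**The case against.** The strongest reply is that nothing here is wrong: Bonferroni after an omnibus test is valid and conservative, and preferring a sharper method is a matter of taste. The first half stands in full. A reader might infer that the plan mishandles its error rate; it does not. What remains is a power loss that one sentence removes.

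The second reply is that the extra strictness may be doing useful work across the two primary outcomes, because the 0.05 is called global. Step 7 shows this is partly right: at 0.05 per outcome, the closed test would let the chance of a false device claim reach about 9.8%. But the plan's rule does not reliably hold 5% across both primaries either. With all arms equal on both outcomes, and the outcomes independent, it gives 1 − (1 − 0.042)² = 0.082. If joint control is meant, the alpha should be split openly. The gain over the plan's present rule is then only about 1 and 5 points.

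Third, the three-pair family is my assumption. Item 27a speaks of changes within and between groups and says the analyses will likely take this form. If within-group tests also count, the correction is harsher and the loss larger.

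Fourth, it is tempting to say that the stricter threshold secures the expected finding of no device difference. The documents do not support that as a motive or as the main weakness. Reading non-significance as similarity is a separate issue that a 0.05 threshold does not cure: power for a 0.70 SD device difference stays at 0.38.

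**Conclusion.** The point holds as a cheap improvement in efficiency. For the between-arm comparison of pre-post change in one outcome, Bonferroni after the omnibus test is valid but needlessly strict in a three-arm trial.

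The logical part rests on no assumption beyond valid component tests. The size does rest on assumptions: three pairs, equal effects in both training arms, normal change scores and rho = 0.5. On that basis the YBT loss is about 8 points per training-versus-control contrast and 14 for both at the target of 12 per arm. At 11 per arm, over rho from 0.7 to 0.3, it ranges from roughly 3 and 6 points to 11 and 19. The direction does not change.

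A reader might extend the control claim to the whole trial. It does not reach that far: it covers one outcome at one time point. It does not cover the two primaries jointly without an alpha split, the FAAM time points, or the many gait parameters.

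**What to change.** Before unblinding, replace the Bonferroni wording in item 27a for the between-arm comparison of pre-post change in YBT and MBESS with: *If the omnibus between-group test is significant at the alpha assigned to that outcome, each of the three pairwise comparisons is tested at the same alpha.*

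- For the YBT, use the group-by-time interaction as the omnibus test and contrasts from the same model.
- For the MBESS, use Kruskal-Wallis on the change scores, then rank-sum tests re-ranked within each pair. Comparisons on joint ranks depend on the third arm and do not fit the closed-test argument.
- State the alpha assigned to each primary. If the global 0.05 is meant to cover both, use 0.025 each.
- Claim familywise control only within one outcome at one time point.

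The cost is a sentence or two of analysis wording and notice to the ethics committee and registry under item 31; no participants are added. There are two downsides. No pair can be declared different unless the omnibus test is significant, and matching simultaneous confidence intervals are not automatic. Bonferroni-adjusted intervals can still be reported alongside.

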#### Secondary outcome measurements

##### Function of the ankle joint

The German version of the Foot and Ankle Ability Measure (FAAM) questionnaire is a validated patient-reported outcome measure to identify functional limitations in individuals with CAI [32–34]. Twenty-one items relate to the Activities of Daily Living (ADL) subscale (FAAM-ADL) and eight items relate to the Sport subscale (FAAM-Sport) [35]. For each item, the possible responses range from 0 “no problems” to 4 “unable to do anything.” The score for each item in each subscale is summed (maximum score for the ADL subscale = 84; maximum score for the Sport subscale = 32). The sum is divided by the maximum score and then multiplied by 100. A resulting maximum score of 100 represents no functional limitation in each subscale. In patients with chronic ankle instability, FAAM-ADL and FAAM-Sport scores of <90 and <80, respectively, are considered to represent functional disability. The questionnaire is also suitable for recording changes over time. The minimum detectable change (MDC) is ±5.7 points for the ADL subscale and ±12.3 points for the Sport subscale [35]. The difference in change between groups is assessed and calculated using nonparametric statistical analysis. The aggregation method is median and interquartile range, and measurements are taken before and after the 6-week intervention, as well as at the 4- and 12-week follow-ups.

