##### Gait biomechanics

In order to assess the gait biomechanics, a 3D gait analysis is performed in the Movement Laboratory of the Niederrhein University of Applied Sciences using two force plates (Bertec, Columbus, OH, USA) with a sampling frequency of 1000 Hz, including a low-pass filter of 500 Hz, and a 10-camera motion analysis system (Qualisys, Göteborg, Sweden), which captures kinematic data at 340 Hz. The two force plates are integrated into a 10-m-long walkway and are later used to detect touch down and toe off events of the foot during gait. Prior to the gait analysis, the measurement system is calibrated according to the manufacturer’s specifications. Then, 26 retro-reflective markers according to the Istituti Ortopedici Rizzoli (IOR) lower body marker set are placed on bony reference points with double-sided tape to record the participants’ gait kinematics [36]. The IOR marker set for the lower body is chosen over other specific marker sets, such as the Oxford foot model and the modified Rizzoli foot model, because Qualisys recommends it and it is well-established in clinical settings. This study focuses on assessing general spatiotemporal gait parameters and the kinematics of major lower extremity joints relevant to activities of daily living and sports, rather than fine movements between the forefoot and rearfoot. The latter may be of interest when specific questions arise regarding ankle and foot joint movements. A static reference measurement is taken from each participant, which is later used for scaling purposes. Participants are then instructed to walk across the walkway at their self-selected walking speed and five valid right and left trials are recorded. Kinematic and kinetic data are processed using QTM Qualisys Track Manager—software, version 2022.2 (Qualisys, Göteborg, Sweden). Lower extremity joint angles, ground reaction forces, joint moments, and spatiotemporal gait parameters are presented in a gait analysis report based on a template by Baker et al. [37]. Relevant gait parameters are vertical, antero-posterior and mediolateral ground reaction forces (N), ankle, knee and hip angles (°), and cadence (steps/min), step length (m), stride length (m), stride width (m), and gait speed (ms−1). In addition, data are processed using the visual 3D software (©HAS-Motion, Canada). Instrumented gait analysis is considered reliable, with mean intraclass correlation coefficients (ICC) ranging from 0.95 to 0.97, mean standard error of measurement (SEM) values ranging from 2.01 to 2.47 degrees, and mean MDC values ranging from 5.86 to 7.02 degrees, and represents the gold standard for gait assessment in individuals with gait abnormalities [38, 39]. For all gait parameters, the difference in change between the groups is assessed and calculated using parametric statistical analysis. The method of aggregation is mean ± SD, and the measurements are taken before and after the 6-week intervention.

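### Bonferroni on the post hoc tests does not make 0.05 global across at least 13 secondary measures for which significance is also hypothesised

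*Protocol article*

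**What the plan says.** Statistical methods {27a} handles gait as a single secondary outcome: "for the secondary outcome of gait biomechanics, the significance of differences in post-intervention change within and between groups will likely be analyzed using repeated measures" ANOVA, followed by Bonferroni-corrected post hoc tests. FAAM gets Friedman or Kruskal-Wallis tests, again with Bonferroni on the post hoc tests. The same section adds: "The global significance level is set to" 0.05. It does not say whether that level applies to each test, to each outcome or across outcomes.

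The Gait biomechanics part of Outcomes {16} shows how many measures stand behind that one label: "Relevant gait parameters are vertical, antero-posterior and mediolateral ground reaction forces (N), ankle, knee and hip angles (°), and cadence (steps/min"), and then "step length (m), stride length (m), stride width (m), and gait speed". It commits to testing all of them: "For all gait parameters, the difference in change between the groups is assessed and calculated using parametric statistical analysis". The part on ankle function gives the FAAM two subscales, ADL and Sport, and "measurements are taken before and after the 6-week intervention, as well as at the 4- and 12-week follow-ups".

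Objectives {10} puts gait and joint function in the same sentence as the primaries: "To determine whether the outcomes of dynamic balance, postural stability, gait biomechanics, and joint function improve in the intervention group and the balance training group". It goes on to ask about a significant difference from control. Its first hypothesis predicts significant improvement in outcomes without separating primary from secondary. The Discussion names the primary and the secondary measures and then hypothesises significant improvement in all of them.

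**The concern.** A Bonferroni correction confined to post hoc tests handles the pairwise comparisons within one measure. It does nothing about the number of measures. If global means per outcome, error is uncontrolled across at least 13 secondary measures. If it means across outcomes, none of the procedures described achieves it. Either way the stated level and the stated procedure do not match.

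This matters because the hypotheses ask for significance on these measures and the protocol does not call them exploratory. With 12 participants per arm and many gait variables, an isolated chance difference on one of them could be reported as a significant training effect.

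**Working it through.** **Count of measures (Outcomes {16}).**
- Gait: 3 ground reaction force components + 3 joint angles + cadence + step length + stride length + stride width + gait speed = 11.
- FAAM: 2 subscales.
- Total: 11 + 2 = 13. This is a minimum. It takes one value per joint angle and one leg, and it leaves out the within-group tests. FAAM is counted once per subscale.

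**The plan's own figures.** The protocol gives no error rate for the secondary outcomes, so there is none to reproduce. Its one design figure, 33 participants in Sample size {19} (*f* = 0.33, power 0.9, alpha 0.05), does reproduce as a group-by-time interaction with 3 groups and 2 times if the correlation between repeated measures is taken as 0.5 (assumed, not stated). The noncentrality is f² × N × 2/(1 − 0.5), with 2 and 30 degrees of freedom, and power is 0.9075. The calculation concerns the YBT composite only, so nothing below changes it.

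**Independent tests.** P(at least one false positive) = 1 − (1 − 0.05)^k.
- k = 11: 1 − 0.95^11 = 0.431.
- k = 13: 1 − 0.95^13 = 0.487.

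**Correlated tests.** The protocol gives no correlations among these measures, so equal correlations of 0, 0.5 and 0.8 are assumed. The simulation has no true effect, three arms of 12 and normally distributed change scores, with a one-way F test on change at 0.05 for each measure. With two time points this is the same test as the group-by-time interaction. For FAAM it stands in for the planned rank test. Post hoc contrasts use Bonferroni for three pairwise comparisons, 0.05/3 = 0.0167 each. Three events were counted:

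| Event on at least one measure | k | corr. 0 | corr. 0.5 | corr. 0.8 |
|---|---|---|---|---|
| Omnibus test significant | 11 | 0.43 | 0.32 | 0.19 |
| Omnibus test significant | 13 | 0.48–0.49 | 0.35 | 0.20 |
| Omnibus plus at least one training-versus-control contrast | 11 | 0.29 | 0.21 | 0.13 |
| Omnibus plus at least one training-versus-control contrast | 13 | 0.33 | 0.24 | 0.14 |
| Omnibus plus both training-versus-control contrasts, same direction | 11 | 0.03 | 0.02 | 0.01 |
| Omnibus plus both training-versus-control contrasts, same direction | 13 | 0.03 | 0.02–0.03 | 0.02 |

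Where two values stand, separate runs differed by simulation error. Repeating the omnibus simulation with 11 per arm gives nearly the same rates (0.43, 0.32 and 0.19 for 11 measures).

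**After a change.** If secondary results carry no significance claim, no threshold is needed. If control across all 13 were wanted instead, a Bonferroni level would be 0.05/13 = 0.0038, and 1 − (1 − 0.0038)^13 is about 0.049 for independent tests.

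**The case against.** Several points on the other side stand.

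- **The joint hypothesis is hard to meet by chance.** Objectives {10} predicts that both training arms beat control. One significant three-arm test does not show that, and the post hoc tests are corrected. A reader might infer that a chance gait finding would confirm the trial's stated hypothesis. On one measure that happens only about 1% to 3% of the time. The exposure is to an isolated significant result.
- **A chance finding is not shown to be likely.** For 13 measures every rate is below one half. The top of the range assumes independence, which is implausible here: gait speed is the product of cadence and step length, and a stride is made of two steps.
- **Testing each measure at 0.05 is inferred.** The protocol leaves the scope of its alpha open.
- **Separate FAAM tests at three times are not stated.** A Friedman test spans the time points in one test, with corrected follow-up comparisons. A Kruskal-Wallis test takes one value per person, so the between-group analysis over time is unclear, but the count of 13 does not depend on it.
- **Gait and FAAM are labelled secondary.** A reader might infer that the protocol makes them confirmatory, or puts them level with the primaries. It does neither: it never uses that word, and the Discussion keeps the two classes apart. Leaving secondary outcomes without family-wise control is common practice.

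It could also be said that ranking of secondary outcomes belongs in the analysis plan, which is not shown. That would answer silence, but the article is not silent. It names the tests, the correction, the place where the correction applies and a global alpha, and it hypothesises significance on every outcome. Those statements do not fit together as written.

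**Conclusion.** The point holds as a mismatch between the stated global 0.05, a correction limited to post hoc tests, and hypotheses of significance on at least 13 secondary measures. If each omnibus test is run at 0.05, the chance of at least one false-positive omnibus result is about 20% to 49%, roughly 4 to 10 times the stated level (0.20/0.05 = 4; 0.49/0.05 = 9.8). At least one spurious training-versus-control contrast has a chance of about 13% to 33% over the 11- and 13-measure cases.

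These sizes rest on the per-test reading of alpha, equal correlations between 0 and 0.8, normal change scores and 12 per arm. Extra angle planes, both legs or within-group tests would raise them. The point concerns what may be claimed from gait and FAAM. It does not touch the primary analyses or the sample size.

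**What to change.** - In Objectives {10} and the Discussion, limit the hypotheses of significant improvement to the primary outcomes, YBT and MBESS.
- In Statistical methods {27a}, describe gait and FAAM as supportive, reported as between-group differences with 95% confidence intervals and no confirmatory claim.
- In the same section, state that the 0.05 level and the Bonferroni correction do not control error across the secondary outcomes.

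A short list of pre-named secondary measures with its own multiplicity procedure is possible if the sponsor wants a secondary claim, but it is optional.

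The cost is wording only, best settled before the data are analysed. No participants or measurements are added. The small downside is that gait and FAAM results can no longer be presented as confirmed.

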**Methods:**

This study is a prospective, single-center, interventional, randomized controlled trial with two comparison groups, either a usual balance training group or a control group. Individuals (18–44 years) with a self-reported ankle instability, a history of at least one ankle injury at least 12 months ago with typical signs of inflammation, two or more episodes of “giving way” within the previous 6 months, and a Cumberland Ankle Instability Tool score ≤ 24 are included. Exclusion criteria include acute injury, lower extremity surgery or fracture, neurological disease, chronic overuse injuries such as Achilles or patellar tendinopathy, and current participation in a targeted ankle rehabilitation program. The primary outcome measures are dynamic balance as measured by the Y-Balance Test and postural stability as assessed by the Modified Balance Error Scoring System. Secondary outcome measures include gait biomechanics measured by 3D gait analysis and self-reported ankle function assessed by the Foot and Ankle Ability Measure.

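### The stated global 5% level is not held as described: YBT and MBESS are both primary, each has its own overall test, and no rule links them

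*Protocol article*

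**What the plan says.** The abstract states: "The primary outcome measures are dynamic balance as measured by the Y-Balance Test and postural stability as assessed by the Modified Balance Error Scoring System". Table 1 and section 27a repeat the pair, and neither outcome is ranked above the other.

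Section 27a assigns repeated measures ANOVA to YBT and Friedman or Kruskal-Wallis tests to MBESS. Both cover differences within and between groups. The only multiplicity adjustment is "post hoc tests with Bonferroni correction to account for multiple testing". The section then adds: "The global significance level is set to" 0.05.

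The sample size section (19) is based on a 4.6% mean difference "in the composite score of the YBT", with f = 0.33, power 0.9 and alpha 0.05. That gives 33 participants, raised to 36 for dropout. MBESS has no sample size calculation and no stated test level of its own.

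**The concern.** A global level of 0.05 is a claim about the whole set of primary tests. Section 27a says where the correction is applied, and on its natural reading that is within an outcome, after the overall test. Nothing described limits the error across the two outcomes, and the sizing of YBT already uses the whole 0.05.

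With 12 participants per arm and two unranked primary outcomes, a significant MBESS result on its own could be reported as a positive primary finding. The error rate behind that claim would be higher than the one the article states.

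**Working it through.** **Inputs from the article.** Two primary outcomes; global alpha 0.05; three groups, 1:1:1, 12 per group; two measurement times for each primary outcome; YBT sizing with f = 0.33, alpha 0.05, power 0.9 and N = 33.

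**Assumptions, because the article gives no value.** The pre-post correlation of YBT (ρ); the correlation between the two outcomes (r); a 0.05 level for MBESS; and that success on either outcome counts.

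**Step 1: reproduce the stated sample size.** For the group-by-time interaction with m = 2 times, the noncentrality is λ = f² × N × m / (1 − ρ), with 2 and N − 3 degrees of freedom. With ρ = 0.5, λ = 0.33² × 33 × 2 / 0.5 = 14.37. Power at alpha 0.05 is 90.7%, and 33 is the smallest N that reaches 90%. The stated figure is reproduced, with the full 0.05 spent on YBT.

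**Step 2: error across the two outcomes.** With both overall tests at 0.05:
- independent outcomes: 1 − 0.95² = 0.0975
- upper bound under any dependence: 0.05 + 0.05 = 0.10

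The effect of correlation was checked by simulating null data with 12 per group and 200,000 replicates. YBT change was tested by ANOVA (with two time points this is the interaction test) and MBESS change by Kruskal-Wallis. The data were continuous and had no ties.

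| Assumed r | At least one false positive |
|---|---|
| 0 | 9.4% |
| 0.3 | 9.3% |
| 0.5 | 9.1% |
| 0.7 | 8.4% |
| 0.9 | 7.2% |

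The 5% level is exceeded throughout. Within-group tests, which section 27a also plans, are not counted here.

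**Step 3: could Bonferroni be meant to span both outcomes?** YBT would then be tested at 0.025, and family error under independence would be 1 − 0.975² = 4.94%. But section 19 sizes YBT at 0.05. For the interaction test at 0.025:

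| Assumed ρ | N for 90% at 0.05 | N for 90% at 0.025 | Power at 0.025, N = 33 | Power at 0.025, N = 36 |
|---|---|---|---|---|
| 0.3 | 44 | 52 | 68.2% | 73.2% |
| 0.5 | 33 | 38 | 84.3% | 88.1% |
| 0.6 | 27 | 32 | 92.2% | 94.7% |

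Of these three values, only ρ = 0.5 returns the article's own 33. At that value a split needs 38 evaluable participants (39 with equal groups), more than the target of 36. On this reading sections 19 and 27a disagree about the level for YBT.

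**The case against.** **The 0.05 level for MBESS is not written down.** A reader might infer that the article explicitly tests each primary outcome at 0.05. It does not. For YBT the level is supported by the sample size section; for MBESS it follows only from the absence of a split. The size of the Bonferroni family is not given either. This stands, and the figures above are conditional on it.

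**The detail may be elsewhere.** The article is condensed, says the tests will likely be used, and points to the registry for the protocol and analysis plan. Silence on alpha allocation alone would be no finding. Here, though, the article asserts a global level and says where its correction sits, and the two do not match.

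**The success rule is open.** Inflation arises only if either outcome suffices. The Objectives and Discussion expect improvement across the outcomes, which leans towards a joint expectation. But an expectation is not a decision rule, and none is stated. The article also hypothesises no difference between the two training groups, so the inflation bears mainly on comparisons with control.

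**The size is easy to overstate.** A reader might infer that the error rate roughly doubles. That holds for low to moderate correlation only. Both outcomes measure balance in the same people, so higher correlations, and a rate nearer 7%, cannot be excluded.

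**Gait is a separate matter.** A reader might count gait parameters and infer that a chance finding is likely. The documents support no such figure: planes and summary points for joint angles are not specified, several parameters depend on one another, and gait is secondary with no confirmatory claim.

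**Conclusion.** The point holds in conditional form. As described, the tests of the two primary outcomes do not deliver the stated global 5%. If MBESS is tested at 0.05 and success on either outcome counts, the chance of at least one false-positive primary overall test lies between about 7% (correlation 0.9) and 9.75% (independence) over the range examined, and cannot exceed 10%. If the article instead means Bonferroni to cover both outcomes, the error claim can be met, but the YBT sample size was then calculated at a different level. Either way the two sections need to be reconciled. This should be corrected because it governs the primary conclusion.

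**What to change.** Name one decisive between-group test per primary outcome: for YBT, the group-by-time interaction on the composite score; for MBESS, the Kruskal-Wallis test on change. Naming them matters because section 27a plans within-group and between-group tests, and a sequence without a named first test controls nothing.

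Then fix the order. Test YBT at 0.05, and test MBESS confirmatorily at 0.05 only if YBT is significant. If YBT has no true effect, a false claim needs a false-positive YBT result (5%). If YBT has a true effect, the only false claim left is on MBESS (at most 5%). Label within-group tests, the Foot and Ankle Ability Measure and gait as supportive or exploratory.

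This leaves the YBT sample size as it is. The costs are that MBESS is not confirmatory if YBT fails, and that the change must be notified to the ethics committee and registry under the protocol amendments section. Enrolment began in July 2023, so it should be settled before any group-level analysis.

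Two alternatives also hold 5%, but either could lower the power stated for YBT. Under Holm, YBT may have to pass at 0.025, where power with 36 participants is 88.1% against 93.3% at 0.05 (ρ = 0.5 assumed). Under a both-must-succeed rule, overall power cannot exceed that of YBT and also depends on MBESS, for which the article gives no power.
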